## Methods

### Study Design and Setting

This multicenter, double-blind, 16-week RCT will be conducted from August 2019 to September 2023 in 4 clinical centers: The Second Affiliated Hospital of Yunnan University of Chinese Medicine, The Sports Trauma Specialist Hospital of Yunnan Province, Kunming Hospital of Traditional Chinese Medicine, and ShengAi Hospital of Traditional Chinese Medicine. A total of 92 eligible participants with AO will be assigned to 1 of 2 groups (catgut embedding at acupoints or nonacupoints) using central randomization (1:1 allocation ratio). Every participant will receive a 12-week intervention period and a 4-week follow-up. The flowchart of this study is shown in Figure 1.

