### Recruitment and Randomization

All participants with eligible AO will be recruited from the 4 hospitals and the community. Recruitment methods mainly include posters, public notice boards, and WeChat public numbers in hospitals and communities. The randomization sequence will be generated by the Clinical Research Center of Yunnan University of Chinese Medicine using a computerized random number generator and placed in opaque envelopes. Stratified randomization will be performed for the 4 clinical centers. To ensure allocation concealment, randomization will be performed by an independent researcher. The research assistant will open the envelope when the participant begins treatment to determine the assigned group and will not disclose grouping information under any circumstances. The acupuncture therapist will be responsible for manipulation only.

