### Sample Size Calculation

According to the existing literature [45], the mean BMI of simple obesity was 32.30 kg/m^2^, whereas after 12 weeks and 6 treatment of acupuncture combined with a low-energy diet, the mean BMI was 30.98 kg/m^2^, and the improvement value was 1.32 kg/m^2^. In contrast, the improvement value was 1.02 kg/m^2^ in a control group with a variation from 32.74 kg/m^2^ to 31.73 kg/m^2^ when treated by sham acupuncture combined with a low-energy diet, and the SD of the 2 groups was 0.31 kg/m^2^. In this project, the expected improvement value of the mean BMI of the Shu-Mu acupoints embedding group after treatment is 1.14 kg/m^2^ and that of the nonacupoints embedding group is 0.9 kg/m^2^, with the SD of each group being 0.31 kg/m^2^. The significant level is ɑ=.05, and the power of a test is 1 – β = 0.95. The sample size is 84 as calculated by German G*power software 3.1 [46]. According to the 10% dropout, the total sample is 92 cases, and 46 cases will be assigned to each group.

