### Outcomes and Assessment

#### Primary Outcome

The primary outcome is the change of WC every 2 weeks, from baseline to end points. To collect the measurements, participants will stand their body upright, feet at shoulder width. An inelastic, 1-mm minimal tapeline will be used, set on the midpoint between the upper border hipbone and lower border 12th rib of the right midaxillary line. At the end of normal exhalation, they will be measured around the abdomen in the horizontal direction and without pressing the skin. The WC will be measured in millimeters (mm) and accurate to 1 mm.

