### Statistical Analysis

All data will be analyzed by SPSS statistical software (version 19.0; IBM Corp). The clinical outcomes and baseline characteristics are based on the intention-to-treat population, which will include participants who have received at least one treatment. Continuous variables will be shown as the mean and SD, whereas the nonnormally distributed variables will be presented as the median and IQR. Categorical variables will be described as numbers and percentages. The normality of continuous variables will be determined using the Shapiro-Wilk test, Kolmogorov-Smirnov test, skewness, and kurtosis. The homogeneity of continuous variables will be determined by *F*-test, Brown-Forsythe, and Bartlett tests. Comparisons between groups will be made using independent samples 2-tailed *t* tests or nonparametric tests (Mann-Whitney *U* test). Repeated measures within groups (≥3) will be analyzed using one-way ANOVA or nonparametric (Friedman) tests. Paired 2-tailed *t* tests or nonparametric tests (Wilcoxon test) will be used for within-group pre-post comparisons. For categorical data, the chi-square test will be used to assess the significance of differences. Values of *P*<.05 will be considered significant using a 2-sided test.

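### The between-group comparison is an unadjusted t test or Mann-Whitney test with neither fixed for the primary outcome; one prespecified model with baseline waist circumference and centre would be firmer and somewhat more precise

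*Protocol article*

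**What the plan says.** All references are to the protocol article.

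- **Between-group test** (Statistical Analysis): "Comparisons between groups will be made using independent samples 2-tailed" t tests or, as the nonparametric alternative, Mann-Whitney U tests. No covariate, stratum term or between-group longitudinal model appears. The repeated-measures methods in that section are for comparisons within a group.
- **Checks listed before it** (same section): "The normality of continuous variables will be determined using the Shapiro-Wilk test, Kolmogorov-Smirnov test, skewness, and kurtosis". Three homogeneity checks follow. No thresholds are given, and no rule for when the checks disagree.
- **Primary outcome** (Primary Outcome): "The primary outcome is the change of WC every 2 weeks, from baseline to end points". No single visit is named, and no test is assigned to this outcome.
- **Randomisation** (Recruitment and Randomization): "Stratified randomization will be performed for the 4 clinical centers". Study Design and Setting adds that participants are assigned "using central randomization (1:1 allocation ratio").
- **Available data** (Table 1): WC is recorded at weeks -1 and 0 and at eight later visits, weeks 2 to 16.

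**The concern.** There are two separate weaknesses.

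1. **The analysis does not use what the design provides.** Stratifying by centre tends to balance the arms within centres, so differences between centres largely drop out of the treatment contrast. An unadjusted test still counts those differences in its standard error. Likewise, a change score subtracts baseline with a fixed coefficient of one. It leaves change correlated with baseline whenever the baseline-to-follow-up correlation is below one, and covariate adjustment removes that remainder.

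2. **The primary test is not fixed.** The t test compares means and the Mann-Whitney test compares rank distributions. Which of them is the primary result seems to depend on normality checks made on the trial data, and could differ from one visit to another. The effect being estimated is then not settled in advance.

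At stake are some precision in a trial of 92 participants and a clear statement of which result counts. The validity of a positive finding is not at stake.

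**Working it through.** **What the plan gives.** There is no effect size, SD or correlation for WC, and no between-centre variance. The only sizing figures are for BMI improvement: difference 1.14 - 0.9 = 0.24, SD 0.31, hence d = 0.24/0.31 = 0.774, power 0.95, stated total 84 before dropout. On these inputs a two-sided t test at 0.05 needs 45 per arm, or 90 in total, so 84 is not reproduced. Rounding d to 0.8 does give 84. That is a separate matter and nothing below depends on it.

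**Step 1: baseline as a covariate.** Let s be the SD of WC at each visit (assumed equal) and rho the correlation between baseline and follow-up.

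- Variance of a change score: 2s²(1 - rho)
- Residual variance under ANCOVA: s²(1 - rho²)
- Ratio: (1 - rho²) / [2(1 - rho)] = (1 + rho)/2

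| Assumed rho | Ratio | 92 / ratio | Equivalent extra participants |
|---|---|---|---|
| 0.7 | 0.85 | 108.2 | about 16 |
| 0.8 | 0.90 | 102.2 | about 10 |
| 0.9 | 0.95 | 96.8 | about 5 |
| 0.95 | 0.975 | 94.4 | about 2 |

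The few degrees of freedom spent on the extra terms are ignored here.

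**Step 2: centre.** Let c be the share of variance in WC change that lies between centres, with the arms balanced within centres. The true variance of the treatment contrast is then (1 - c) times what the unadjusted test assumes, so its actual two-sided alpha is 2[1 - Φ(1.96/√(1 - c))].

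| Assumed c | 1.96/√(1 - c) | True alpha |
|---|---|---|
| 2% | 1.980 | 0.048 |
| 5% | 2.011 | 0.044 |
| 10% | 2.066 | 0.039 |

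The error is in the conservative direction. The relevant quantity is how far centres differ in WC *change*, not in WC level.

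**Step 3: simulation.** Settings: normal data, 42 per arm, four centres balanced by arm, 3,000 runs per cell, rho = 0.8, true effect 0.6 SD of change. The normality-based choice used Shapiro-Wilk in each arm at 0.05.

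| Method | Power, no centre effect | Power, c = 10% |
|---|---|---|
| t test | 0.78 | 0.79 |
| Mann-Whitney | 0.74 | 0.77 |
| Choice by normality test | 0.77 | 0.79 |
| ANCOVA with baseline and centre | 0.82 | 0.85 |

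At rho = 0.9 with no centre effect the gain shrinks to 0.78 against 0.79. Under the null with no centre effect, the normality-based choice rejected in 4.8% to 5.1% of runs across rho = 0.5, 0.8 and 0.9. The Monte Carlo standard error is √(0.05 × 0.95/3000) = 0.4 percentage points, so no inflation is visible. Only normal data were simulated.

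**The case against.** The strongest case for the plan is that an unadjusted t test on change in a 1:1 randomised trial is valid, so adjustment only improves efficiency, perhaps by little. The plan's own BMI figure points that way. With SD of change 0.31 and cross-sectional SD s (assumed), the ratio in step 1 becomes 1 - 0.31²/(4s²): 0.976 at s = 1, 0.994 at s = 2 and 0.997 at s = 3. That would be worth about two participants at most. This stands as a caution about size, although it concerns BMI and not WC.

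Four stronger readings are tempting, and the document does not support them:

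- **That baseline WC is ignored.** It is not. The outcome is a change from baseline; only covariate adjustment is absent.
- **That choosing the test after seeing the data inflates type I error or lets the team pick the favourable result.** The simulation shows no inflation. The Blinding and Informed Consent section also keeps those handling the statistics blind to assignment, which limits directional selection. Moreover, the text implies, but never states outright, that the normality results decide the test.
- **That separate tests at each visit drop participants who missed it.** The article describes neither visit-by-visit testing nor the handling of missing visits. The latter is commonly left to the full protocol or analysis plan.
- **That a repeated-measures mixed model at a particular week is required.** An ANCOVA at one named time point meets the concern.

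None of this supplies the missing selection rule or assigns a test to the primary outcome. Nor does it give a reason to leave out a stratification factor and a baseline value that are already collected.

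**Conclusion.** The point holds as a low-cost improvement to a stated analysis, not as a flaw that invalidates it.

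- **Unfixed test:** this follows from the text alone. Two tests of different hypotheses are offered, and neither is assigned to WC change. That normality results decide between them is the natural reading, not an explicit statement.
- **Baseline:** the precision lost by using a change score without adjustment is 2.5% to 15% of the variance for assumed rho of 0.95 to 0.7. It is modest if WC correlates strongly over time, as it may.
- **Centre:** omitting it costs power to the extent that centres differ in WC change. For assumed shares of 2% to 10%, true alpha is about 0.048 to 0.039 in place of 0.05. A significant result would remain valid.

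The sizes rest on an assumed correlation, an assumed centre share, equal variances at the two time points and balance of arms within centres. None of these figures is in the protocol.

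**What to change.** Before unblinding, prespecify one primary analysis along these lines:

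- WC change from baseline at one named time point, chosen and stated by the sponsor, is compared between groups in a linear model with treatment, baseline WC and centre. State which pre-treatment measurement (week -1 or week 0) is the baseline.
- The adjusted mean difference is reported with its 95% CI and a two-sided p-value at 0.05.
- This model is used whatever the normality and homogeneity tests show. The Mann-Whitney test is kept as a sensitivity analysis only.
- Body weight, BMI, hip circumference and appetite score use the same model, each with its own baseline value.

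A mixed model for repeated measures over all visits, with the same covariates plus visit and treatment-by-visit, is an acceptable alternative. The effect must still be read at the named time point. An unstructured covariance over eight post-baseline visits has 8 × 9/2 = 36 parameters, so that option needs a stated fallback if the model does not converge.

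The cost is analysis wording only. SPSS, the package already named, fits both models, and all the data are in the current schedule.

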### Strengths and Limitations

First, this study is a multicenter RCT designed to investigate the efficacy and safety of ACE in AO with a relatively long study period, and the results will provide powerful evidence for the clinical application of ACE in the treatment of obesity. Second, participants’ diet and exercise will not be intervened, which will allow participants to maintain their original lifestyle habits throughout and maximize the efficacy of ACE. Finally, to maintain the success of the double-blind method, contact between participants from different groups will be avoided. The acupuncturist, data evaluator, and statistician will also be hidden from the group assignment, which will minimize possible bias in the results.

Limitations of this study are as follows. First, the relatively short follow-up period of this study may not be comprehensive enough to assess the durability of ACE efficacy. Second, the selection of nonacupuncture acupoints as an intervention in the control group in this study may inevitably produce some efficacy as well [62,63]. Third, only patients with AO are selected as the study population in this study, and further studies on different types of obesity will be conducted at a later stage.

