### Conclusions

In summary, our trial aims to investigate the difference in the effectiveness of catgut embedding at acupoints and catgut embedding at nonacupoints in patients with AO. This finding will provide reliable evidence to support whether ACE is an effective and safe treatment for AO.

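### One-way ANOVA is named for repeated measures within an arm: read literally it ignores within-person correlation and can hardly detect change, and the planned conclusion is wider than the randomised contrast

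*Protocol article*

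**What the plan says.** The primary outcome section reads: "The primary outcome is the change of WC every 2 weeks, from baseline to end points". Table 1 lists WC at allocation (week 0) and at weeks 2, 4, 6, 8, 10, 12, 14 and 16, so each participant contributes nine values from allocation onward.

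The Statistical Analysis section sets out three kinds of comparison:

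- Between groups: independent-samples t tests or Mann-Whitney tests.
- Within a group, three or more measurements: "Repeated measures within groups (≥3) will be analyzed using one-way ANOVA or nonparametric (Friedman) tests".
- Within a group, two measurements: "Paired 2-tailed *t* tests or nonparametric tests (Wilcoxon test) will be used for within-group pre-post comparisons".

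One threshold covers all of them: "Values of *P*<.05 will be considered significant using a 2-sided test". None is named as the basis for the conclusion. The assumption checks listed are for normality and for homogeneity of variance; sphericity is not mentioned.

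On interpretation, the Objective is the difference between acupoint and nonacupoint embedding. The closing Conclusions section repeats that aim and then adds: "This finding will provide reliable evidence to support whether ACE is an effective and safe treatment for AO". The Abstract and the end of the Introduction make the same promise. Strengths and Limitations says of nonacupoint embedding that it "may inevitably produce some efficacy as well".

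**The concern.** An ordinary one-way ANOVA compares visit means against the spread of all values around those means. In repeated measurements on the same people, most of that spread is the stable difference between large and small waists, which has nothing to do with change over time. Leaving it in the error term swamps a real within-arm trend.

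The alternative test for nonnormal data, Friedman, does respect the pairing. Followed literally, the plan would therefore let a normality check decide whether within-person correlation is taken into account at all, and the two branches could give opposite answers on the same data.

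A second matter concerns wording. Both arms receive embedding at 11 points, with the control points 2-3 cm away from the acupoints. Randomisation therefore isolates point location. Whether ACE is effective is a broader question than that contrast can answer in either direction.

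**Working it through.** The plan reports no figure for its within-group analysis, so there is none to reproduce. The check asks how the named test behaves on data of the planned shape.

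**Inputs from the article.** 46 participants per arm (Sample Size Calculation); nine visits (Table 1); two-sided 5% level (Statistical Analysis).

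**Assumed inputs, not in the article.** WC SD of 9 cm at each visit; a straight-line fall of 3 cm from week 0 to week 16; equal correlation ρ between any two visits, varied from 0.5 to 0.95.

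**Step 1: expected mean squares.** The fall per visit is 3/8 = 0.375 cm. The squared deviations of the nine visit means from their average sum to 60 × 0.375² = 8.44. Multiplied by 46 and divided by 8 degrees of freedom, this adds 48.5 to the visit mean square.

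- Visit mean square: 81(1 − ρ) + 48.5.
- Error mean square, ordinary one-way ANOVA: 81.
- Error mean square, repeated-measures ANOVA: 81(1 − ρ).

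The ratios of these expected values are therefore:

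- one-way: (1 − ρ) + 48.5/81 = (1 − ρ) + 0.60
- repeated-measures: 1 + 0.60/(1 − ρ)

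The 5% critical value is about 1.96 for both (8 and 405, or 8 and 360, degrees of freedom).

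| ρ | One-way, no change | One-way, 3 cm fall | Repeated-measures, 3 cm fall |
|---|---|---|---|
| 0.5 | 0.50 | 1.10 | 2.20 |
| 0.8 | 0.20 | 0.80 | 3.99 |
| 0.9 | 0.10 | 0.70 | 6.99 |
| 0.95 | 0.05 | 0.65 | 12.98 |

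The more closely visits are correlated, the further the one-way ratio falls below 1.96, although the data then carry more information about change.

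**Step 2: rejection rates by simulation** (1,000 trials per setting, same assumptions, 3 cm fall).

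| ρ | One-way | Repeated-measures, Greenhouse-Geisser | Friedman |
|---|---|---|---|
| 0.5 | 0.066 | 0.51 | 0.485 |
| 0.8 | 0.003 | 0.95 | 0.924 |
| 0.9 | 0.000 | 0.999 | 0.999 |
| 0.95 | 0.000 | 1.0 | 1.0 |

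Further runs of the 3 cm fall put the one-way rate no higher than 0.010 at ρ = 0.8 or more. Under no change, one-way ANOVA rejected 0.0005 of the time at ρ = 0.5 and 0.000 at ρ = 0.8 or more, instead of 0.05.

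**Step 3: does the equal-correlation assumption drive this?** With correlation that decays over time (AR(1)) and a fall of 0.3 SD (2.7 cm at SD 9 cm), one-way ANOVA rejected 0.055 of the time at 0.9 and 0.005 at 0.97. The Greenhouse-Geisser test rejected 0.40 and 0.81. The loss is smaller at 0.9 but still large. Under no change, repeated-measures ANOVA without a sphericity correction rejected 0.118 and 0.110 of the time; with the correction, 0.054 and 0.045. The correction is therefore needed.

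**Step 4: the paired pre-post test.** Under no change, the paired t test rejected between 0.045 and 0.056 of the time at every correlation tried. It holds its level.

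**The case against.** The strongest reply is that the sentence is only loosely worded. It calls the data repeated measures, and it pairs the ANOVA with Friedman, a related-samples test; the counterpart of an independent-groups ANOVA would be Kruskal-Wallis. A one-way repeated-measures ANOVA is a plausible intended meaning, and the article condenses a fuller plan. This stands as a reading of intent. It does not make the text correct: the article names a different procedure and mentions no sphericity check, and an analyst following the words would run the wrong test.

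A reader might also infer that the pre-post tests are invalid for correlated visits. They are not; paired t and Wilcoxon tests are made for such data.

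A reader might infer that the ANOVA error would falsely credit ACE with efficacy. It works the other way: the literal test almost never rejects.

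A reader might infer that the conclusion will rest on within-group change. No section says so. The Objective, the Sample Size Calculation and the closing Conclusions all frame a between-group comparison, and the limitation of the control is disclosed. What remains is that the within-group tests sit beside the between-group tests at the same threshold, and that the promise about ACE being effective is wider than the contrast behind it.

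**Conclusion.** The point holds as a correction of a named test and of the stated claim. Taken literally, one-way ANOVA on the nine visits is the wrong procedure. Under the assumed SD of 9 cm, linear 3 cm fall and equal correlation of 0.8 to 0.95, it would detect the fall in at most about 1% of trials, against roughly 95-100% for repeated-measures ANOVA and 92-100% for the plan's own Friedman alternative. The SD, fall and correlation are assumptions. At a correlation of 0.5 the gap narrows to 0.066 against 0.51, and with no correlation it disappears.

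The damage is confined to the within-group analysis. The between-group tests and the sample size, which rests on a between-group difference, do not change. Separately, a contrast of point location, with a control that may itself have some efficacy, cannot settle whether ACE is effective: a null result would show no detected location effect, and change within an arm has no untreated comparison.

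**What to change.** In Statistical Analysis, replace one-way ANOVA with *one-way repeated-measures ANOVA with Greenhouse-Geisser correction*, or with a linear mixed model that has visit as a factor. The mixed model has the advantage of keeping participants who miss a visit, which matters because the plan allows for 10% dropout.

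State that all within-group change, including the paired pre-post results, is descriptive, and that the between-group comparison is the only basis for the efficacy conclusion.

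In the Abstract, the end of the Introduction and the Conclusions, word the question as whether embedding at acupoints reduces WC more than embedding at nonacupoints.

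The cost is a different SPSS procedure on the same data and a narrower claim. No new participants or measurements are needed. The planned between-group t or Mann-Whitney tests can stay as they are for this purpose.

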## Results

The start of recruitment began in August 2019 and is expected to end in September 2023.

## Discussion

### Expected Findings

In the past, obesity was considered a problem in high-income countries. However, recent studies reported that the prevalence of obesity is rapidly increasing in low- and middle-income countries [4,48-50]. As a type of obesity, AO is also related to cardiovascular diseases, cancer, and many other diseases [51-54].

ACE is a traditional Chinese medical practice that has been used in clinical practice since the mid-1960s. Compared with other treatments, ACE has the advantages of a short single-treatment time, long effective stimulation time, low impact on daily life, as well as being time-saving and low cost and having few side effects, which are well suited for the fast-paced modern society and become gradually favorable to patients who are obese. As a specific type of acupuncture therapy, ACE has gained substantial attention in the management of obesity in recent years. Research has demonstrated that ACE has a certain impact on obesity. First, it can reduce BW by regulating appetite and food intake. ACE stimulates specific acupoints, promoting the release of neurotransmitters and hormones to regulate feelings of hunger and satiety and ultimately reducing food intake [55]. Second, ACE can improve metabolic function. Studies have shown that acupoint stimulation can affect various physiological processes, including the endocrine, nervous, and immune systems, thus regulating energy and fat metabolism, improving insulin sensitivity, and enhancing blood lipid levels [41]. Additionally, ACE may also have positive effects on obesity by improving psychological well-being and sleep quality, among other factors [56]. However, current research has some limitations, including small sample sizes and inconsistent study designs [57]. Therefore, to better assess the effectiveness and safety of ACE treatment, further high-quality studies with larger sample sizes are needed.

The decrease of several indicators such as BW, WC, BMI, HC, and appetite is not only beneficial to personal health but also helps people who are obese to reshape their bodies [58]. Among them, BMI is the most commonly used indicator in obesity research, but it mainly reflects total body fat and cannot distinguish between fatty obesity and muscular obesity. HC is affected by both sex and age, and changes in abdominal fat cannot be accurately reflected promptly [59]. WC can directly reflect abdominal fat, so we use WC as the main outcome indicator and other related indicators as secondary outcome indicators. According to the classification adopted by the Chinese Medical Association of China in 2019, the inclusion criteria was set as WC ≥90 cm for male individuals and ≥85 cm for female individuals, rather than those of other Asian countries (WC ≥102 cm for male individuals and WC ≥88 cm for female individuals or WC ≥ 90cm for both male and female individuals) [6,60].

The combination of Shu and Mu acupoints is one of the classical methods of acupuncture and is mainly used in clinical practice to treat metabolic diseases of the viscera. According to the identification theory of traditional Chinese medicine, obesity is mainly caused by the dysfunction of the spleen, stomach, and large intestine, so we chose the Shu and Mu acupoints of these 3 internal organs as the treatment prescription. Our preliminary analysis of 175 obesity ACEs in the early stage also found that the existing high-frequency acupoints for obesity ACEs were mainly Shu and Mu acupoints of the spleen, stomach, and large intestine [61].

